**3.8 Sampling Process**

A two-stage multi stage sampling approach will be used as follows:

***3.8.1 First stage: Community selection***

- All communities in the district would be eligible for selection
- A simple random sampling technique of balloting without replacement would be used to select four communities
- In the event that the selected communities are not large enough to give the desired number of at least 108 households and 184 children under five, a simple random technique would be employed to select additional communities until the desired number of household and children are achieved.
- In the event that the communities have more than the desired number of households with eligible children when put together, a quota system would be used to allocate the number of household to be selected per each of the four selected communities.
- In case of large communities, the community would be stratified and uniformly sample from each stratum.

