***3.5.1.2 Inclusion criteria at the participant level;***

1. All children within the eligible household aged 6 to 56 months at baseline.
2. Haemoglobin concentration measured at baseline should be less than 11.0 g/dl.
3. The child should be residing in the selected community for at least the past three month.
4. Must have a legal guardian capable of providing informed consent.

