***3.8.2 Second Stage: Household and individual selection***

The process of obtaining households will be sampled based on the following guidelines:

1. Conduct a quick House and Household Listing in all four selected communities
2. Survey eligible households with the selected village
3. Interview only Household Heads/Spouse (Care givers) per each household
4. All eligible children per selected household would be enumerated and included in the study

At the end of the process a total sample size of at least 184 children and 108 households will be sampled from at least, four communities across the targeted district.

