**3.9 Recruitment of study participants**

Kumbungu district has a 115 communities most of which are farming communities with population below 500 inhabitants and an average of 62 under-five per community. About six communities would be selected by simple random techniques and the a census of under-five within all households obtained. Community entry procedures would be followed and community leaders, assemblyman, and/or chief involved in a stakeholder engagement process. A selected household head and members of the household would be educated on the study procedures and consent obtained from the head of the family. Accent would be obtained from the individual children taking part in the study.

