**3.14 Project Management**

***3.14.1 Reconnaissance visit***

A team led by the PI will conduct a reconnaissance visit to the six targeted communities. This visit will afford the team a good understanding of the project communities. This will also give the PI the opportunity to improve the proposed sampling and field strategies, as well as establish critical contacts with key stakeholders in the project communities.

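### The rule for adding communities counts all under-fives, not the eligible anaemic children the 184 refers to, and the number of communities is given as both four and six

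*Protocol*

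**What the plan says.** Section 3.7 sets a minimum of 92 children per arm (184 in total) and 54 households per arm (108 in total). The household figure is 92 divided by 1.7. The 1.7 is all 7,101 children under five in the district divided by all 4,133 households.

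Section 3.5.1.2 limits participants to children aged 6 to 56 months, with a further condition: "Haemoglobin concentration measured at baseline should be less than 11.0 g/dl". It also requires three months' residence and a guardian able to consent. Section 3.5.2 then removes children with febrile infection, a diagnosed haemoglobinopathy or recent iron.

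Section 3.8.1 fixes the sampling: "A simple random sampling technique of balloting without replacement would be used to select four communities". Communities are added if those drawn are "not large enough to give the desired number of at least 108 households and 184 children under five". If there are more than enough households with eligible children, a quota limits the number taken. Section 3.8.2 says that "at least 184 children and 108 households will be sampled from at least, four communities across the targeted district".

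On the number of communities, section 3.9 says "About six communities would be selected by simple random techniques", and section 3.14.1 plans a "reconnaissance visit to the six targeted communities".

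**The concern.** The trigger uses the right number with the wrong unit. Section 3.7 itself expects 18% of children not to be anaemic, so 184 under-fives cannot supply 184 participants. The field team could draw four communities, find both thresholds met, add none, and then discover at baseline screening that too few children qualify. Households are stratified and randomised from the baseline data (section 3.10), so a shortfall found at that stage is awkward to repair.

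The conflict between four and six communities matters for the same reason: on the protocol's own averages, four falls a little short of the target and six clears it. At stake is whether the trial reaches the sample size on which its stated power rests.

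**Working it through.** **Inputs from the protocol.** 62 under-fives per community (3.9); 7,101 under-fives, 39,341 people, 4,133 households and 115 communities, of which only two exceed 5,000 people (3.1); 82% anaemia with a 20% reduction, design effect 1.03, dropout 5%, contamination 10%, power 80%, two-sided 5% (3.7).

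**Assumption.** The share of under-fives aged 6 to 56 months is not given. Uniform ages give 51/60 = 85%; I show 83% to 90%.

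**The plan's own figure.** Two proportions, 82% v 62%, pooled variance under the null, p̄ = 0.72:
- n = (1.96·√(2·0.72·0.28) + 0.842·√(0.82·0.18 + 0.62·0.38))² / 0.20² = 78 per arm.
- 78 × 1.03 × 1.05 × 1.10 = 92.8, against the stated 92.
- This requires the 20% reduction to be absolute points. A relative reduction (to 65.6%) gives 112 before inflation and does not reproduce 92.

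**Yield if the count is exactly at the trigger (184 under-fives).**
- Anaemia filter alone: 184 × 0.82 = 151.
- Both filters: 184 × 0.85 × 0.82 = 128 (126 to 136 for an age share of 83% to 90%).

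**Yield from four communities of average size.**
- 4 × 62 = 248 under-fives; 248 / 1.718 = 144 households. Both thresholds are passed, so nothing is added.
- 248 × 0.85 × 0.82 = 173 (165 to 190 for anaemia of 78.4% to 90%).

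**Yield from four typical smaller communities.** Two large communities inflate the mean of 62.
- Setting aside at least 2 × 5,000 people leaves at most (39,341 − 10,000)/113 = 260 people in each of the others, on average.
- Under-five share 7,101/39,341 = 18.0%, so about 46.9 under-fives each.
- Four hold 187 under-fives in 187/1.718 = 109 households, just above 184 and 108. Nothing is added.
- Eligible: 187.5 × 0.85 × 0.82 = 131.
- A simple random draw of four misses both large communities with probability (111 × 110)/(115 × 114) = 93%.

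**Yield from six.** Average size: 372 × 0.85 × 0.82 = 259. Typical smaller: 281 × 0.85 × 0.82 = 196.

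**Power.** Effective n per arm = (N/2) × 0.95/1.03, and power = Φ[(d − 1.96·√(2p̄(1−p̄)/n)) / √((p₁(1−p₁)+p₂(1−p₂))/n)]. The last column shrinks the difference by 10% for contamination (80% v 62%).

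| Children enrolled | n per arm, net | Power, 82% v 62% | Power, 80% v 62% |
|---|---|---|---|
| 184 | 84.9 | 83% | 74% |
| 173 | 79.8 | 81% | 71% |
| 131 | 60.4 | 69% | 59% |
| 128 | 59.0 | 68% | 58% |

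**Under-fives needed for 184 eligible.** 184/(0.85 × 0.82) = 264, which is 4.3 average communities or 264/46.9 = 5.6 typical smaller ones, before the other exclusions and refusals.

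**The case against.** The case on the other side has real substance.

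- **Section 3.8.2 promises at least 184 children from at least four communities and includes all eligible children.** This shows the intent, and four plus additions could become about six. But it states a result. The only rule that adds communities is in 3.8.1, and that rule counts under-fives.
- **The quota bullet speaks of households with eligible children.** If eligible means anaemic, and children per household follow a Poisson distribution, the mean per qualifying household is 1.20/(1 − e^−1.20) = 1.72, so 108 households give about 185 children and the target is met before exclusions. Reading 108 households in the trigger the same way, four average communities hold about 101 such households, so more would be added. That reading is sensible, but the trigger does not state it, and the household criterion in 3.5.1.1 asks only for a child aged 6 to 56 months. On that criterion, 108 households give about 168 children (108 × 1.90 × 0.82) and about 80% power.
- **Anaemia may be nearer 90% in the north, as section 1.1 suggests.** Four average communities would then yield about 190, and the shortfall disappears for that draw.

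A reader might infer that the written rules always stop well short of 184, that additions are never triggered, or that stated power is lost in every case. The documents do not support this. Nothing tells the team to stop at 184 under-fives, a small draw would trigger additions, and four average communities keep about 81% power. Nor should 58% power after contamination be put down to sampling alone: the same contrast at the full 184 gives only 74%.

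**Conclusion.** The point stands as a fault in wording with a conditional effect. The trigger in 3.8.1 is stated in the wrong unit: at the plan's own 82% anaemia, 184 under-fives give at most about 151 participants on average, whatever the age distribution.

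The size depends on the draw. The expected shortfall is about 6% with four average communities (173 of 184), which leaves power just above 80%. It is about 29% with four typical smaller communities (131 of 184), which takes power to about 69%. The second case is not remote, since about 93% of draws of four contain neither large community, although the smaller communities will themselves vary in size.

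These figures rest on an assumed age share of 85%, 82% anaemia, 20 absolute points of effect, and no further loss to illness, recent iron, residence or consent. Any such loss lowers the yield. Separately, four and six communities are both stated as the plan, and the sections must be reconciled.

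**What to change.** In sections 3.8.1 and 3.8.2:

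1. State both the trigger for adding communities and the end condition as at least 184 enrolled children who meet 3.5.1.2 and are not excluded under 3.5.2.
2. Say that the 108-household count and the quota refer to households with at least one such child, and that the quota may not take enrolment below 184.
3. Give one number of communities in 3.8.1, 3.8.2, 3.9 and 3.14.1. Six is consistent with the target (about 196 eligible from typical smaller communities, 259 from average ones). Four falls short of it at the plan's 82% anaemia, unless the corrected trigger adds more.

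The cost is protocol wording and possibly listing one or two more communities, which 3.9 and 3.14.1 already foresee. The stated sample size is unchanged. The change should be made before household listing starts.

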***3.8.2 Second Stage: Household and individual selection***

The process of obtaining households will be sampled based on the following guidelines:

1. Conduct a quick House and Household Listing in all four selected communities
2. Survey eligible households with the selected village
3. Interview only Household Heads/Spouse (Care givers) per each household
4. All eligible children per selected household would be enumerated and included in the study

At the end of the process a total sample size of at least 184 children and 108 households will be sampled from at least, four communities across the targeted district.

**3.9 Recruitment of study participants**

Kumbungu district has a 115 communities most of which are farming communities with population below 500 inhabitants and an average of 62 under-five per community. About six communities would be selected by simple random techniques and the a census of under-five within all households obtained. Community entry procedures would be followed and community leaders, assemblyman, and/or chief involved in a stakeholder engagement process. A selected household head and members of the household would be educated on the study procedures and consent obtained from the head of the family. Accent would be obtained from the individual children taking part in the study.

**3.10 Randomization: sequence generation, stratification and blocking**

The data from the baseline survey would be used for sequence generation. Clusters would be stratified by mean household haemoglobin. Using the mean household haemoglobin, the clusters would be stratified into Level I; 10.0 g/dL ≥ Hb ≤ 10.9 g/dL, Level II; 7.0 g/dL ≥ Hb ≤ 9.9 g/dL, and Level III Hb < 7.0 g/dl

Households would be ordered alphabetically using household head’s surname. The ordered alphabetical name would be imported in to a statistical computer software STATA V.11 at the community health department, school of public health, University of Ghana. The program would generate a series of blocks of varying size (four, eight and twelve) for each stratum and allocate the household clusters to study arm randomly within each block [72]. Consent to randomize would be obtained at the cluster level from the household head.

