**3.13 Procedure for Data collection**

A team of trained data collectors would carry out data collection at baseline and end-line. The data collection team would be made up of a physician specialist, optometrist, medical laboratory scientists, nurses and trained nutritionist. The behavioural change intervention would be administered by trained community health nurses who would each be responsible for each community. A three day training would be carried out before baseline assessment and a one-day refresher training prior to end-line assessment. Baseline data and end-line data collection is each estimated to take a week at week zero and thirteen respectively. The data collection team would visit households and administer household questionnaires as well as individual child questionnaires after completing consent and assent procedures. Clinical examinations would be carried out by the physician specialist, the optometrist carry and ophthalmic nurses carry out the eye examination.

A trained phlebotomist would carry out the bloodletting. The nutrition team would carry out the anthropometric assessment, dietary recall and quantification of dietary content of iron, folate, enhancers and inhibitors of iron absorption. Five millilitres of blood samples would be taken for haematological and biochemical analysis. The trained community health nurses would carry out the behavioural change communication intervention at week one, four and eight of the intervention period. Administration of pre-packaged and labelled iron and folic acid syrups would be administered by the community health nurses.

The community health nurses would not be involved in the data collection. The independent data collection team would be blinded to the household randomisation. Other information to be collected would include household characteristics, medication history, details about intake of IFA supplements, adverse events of intervention, out of pocket expenses for adhering to interventions, morbidity and mortality outcomes.

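### Allocation is stratified by household haemoglobin but not by community, although each community has its own nurse: a cheap gain in balance and precision is left unused

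*Protocol*

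**What the plan says.** Protocol 3.10 sets out the allocation. "Clusters would be stratified by mean household haemoglobin", in three levels. "Households would be ordered alphabetically using household head"'s surname, and the program then forms "blocks of varying size (four, eight and twelve) for each stratum". Community plays no part. The only stratification tied to communities is in 3.8.1, and it concerns how households are sampled inside large communities.

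Protocol 3.13 ties staff to place: "The behavioural change intervention would be administered by trained community health nurses who would each be responsible for each community". The same nurses give the supplement in both arms: "Administration of pre-packaged and labelled iron and folic acid syrups would be administered by the community health nurses".

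The number of communities is small and stated in two ways. Section 3.8.1 reads "A simple random sampling technique of balloting without replacement would be used to select four communities", and 3.8.2 also works with four. Section 3.9 reads "About six communities would be selected by simple random techniques", and 3.14.1 also refers to six.

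Under 3.10 and 3.11, the baseline survey feeds the sequence and clusters are recruited before randomisation, so each household's community is on file when the list is made. Section 3.20 names an equal-variance two-sample t-test for mean haemoglobin, without a community term.

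**The concern.** Community and nurse coincide, so local conditions and the way syrup is handed out vary along the same line. Malaria, food supply and syrup administration during the 12 weeks can all influence haemoglobin at the end. Strata built on baseline haemoglobin capture where a household starts, not what happens to its community afterwards. With only four to six communities, one uneven community is not averaged out by many others.

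At stake are the precision of the arm comparison and its face validity. The trial is run once, and a reader who sees one community and its nurse split 2:1 between arms will question the result even if the test is valid on average.

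**Working it through.** **The plan's sample size (3.7).** Taking 82% against 62% (20 points absolute), two-sided 5%, 80% power and unpooled variance gives 76 per arm. Then 76 × 1.03 / 0.95 / 0.90 = 91.6, so 92 per arm, and 92 / 1.7 = 54.1 households. The stated 92 children and 54 households per arm are reproduced. The point below does not change them.

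**Inputs.** From the protocol: 108 households, 54 per arm, 1:1; blocks of 4, 8 and 12 within haemoglobin level; four or six communities; household ICC 0.010. Assumed, because the protocol gives no figure: equal community sizes (27 or 18 households), haemoglobin-level shares of 30/65/5%, and the community ICC.

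**Chance of a lopsided community.** If 54 of 108 households go to each arm without regard to community, the number from one community in one arm is hypergeometric. The probability of a 2:1 or worse split is 0.074 for a community of 27 and 0.196 for one of 18. Treating communities as independent gives 1 − (1 − 0.074)^4 = 0.27 and 1 − (1 − 0.196)^6 = 0.73. Simulation of the actual scheme (20,000 runs) gives 24–25% and 70%. With unequal sizes (assumed 48/30/20/10 and 40/24/16/12/10/6) it gives 41% and 89%.

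**More extreme splits.** A split of 75% or more to one arm in at least one community has probability 0.6% (four equal) or 10% (six equal). A given community falling wholly into one arm has probability about 2 × 10⁻¹⁰ (27 households) or 1 × 10⁻⁶ (18). For a community giving only 6 households it is 2.7%.

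**Bias and type I error.** In simulations with six equal communities (8,000 runs per setting, total SD 1), the mean arm difference without community stratification was within 0.004 of zero. The plain t-test rejected in 4.9–5.1% of runs for community ICC 0 to 0.20.

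**Loss of precision.** Let S be the expected sum over communities of squared differences between the arms' community shares. For C communities of m households, S = C × (2/54)² × [m × ¼ × (108 − m)/107]. For 4 × 27, S = 4 × (2/54)² × 5.11 = 0.028. For 6 × 18, S = 6 × (2/54)² × 3.79 = 0.031. In units of total variance, the unbalanced design has variance ICC × S + (1 − ICC) × 4/n. With community balanced and in the model, the first term drops out. The excess in standard error is √(1 + ICC × S / [(1 − ICC) × 4/n]) − 1. The two values of n bracket the truth: 108 independent household means and 184 independent children.

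| Community ICC | Four communities (n = 108 to 184) | Six communities (n = 108 to 184) |
|---|---|---|
| 0.01 | 0.4% to 0.7% | 0.4% to 0.7% |
| 0.05 | 2.0% to 3.3% | 2.2% to 3.7% |
| 0.10 | 4.1% to 6.9% | 4.6% to 7.7% |
| 0.20 | 9.1% to 15.0% | 10.0% to 16.5% |

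The middle of the six-community ranges is under 1%, about 3%, 6% and 13%. In the simulations, stratified blocks without a community term recovered less: the SD went from 0.193 to 0.193, 0.192 to 0.189, 0.192 to 0.185 and 0.189 to 0.175.

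**Why the analysis term matters.** With stratified blocks but the plain t-test, the simulated type I error fell to 4.4%, 4.3% and 3.6% at ICC 0.05, 0.10 and 0.20. The balance is achieved, but the test does not use it.

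**The case against.** The strongest reply is that this is a design preference. Stratifying on the baseline value of the outcome is legitimate, the comparison is unbiased, and ordinary chance imbalance is already in the standard error. That stands.

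The likely size is also open to challenge. Children of one household share a community, so a household ICC of 0.010 (3.7) caps the community ICC on the scale of that figure, which is anaemia prevalence. If 0.010 is right, the gain is under 1%. That stands too, though 3.7 gives no source for the value. In addition, 3.20 works from each child's change in haemoglobin, so stable differences between communities largely cancel. What remains is what differs between communities during the 12 weeks.

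A reader might infer three stronger things that the protocol does not support:

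- That a whole community and its nurse could end up in one arm. The probabilities above rule this out in practice unless a community contributes only a few households.
- That better counselling by one nurse could mimic a treatment effect. Under 3.3 only LAD (locally available dietary intervention) households are counselled, so imbalance merely changes how nurses are weighted within that arm. Weekly monitoring of the supplement is by a study team member who is not said to be the community's nurse.
- That the noise can be expressed as a share of the 2.6 g/L shift in 3.20. A standard deviation should be set against the total standard error, and that shift is not what the sample size in 3.7 was built on.

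Finally, a community term in the model alone would recover most of the precision. This is partly right. Adjustment without balance costs a variance factor of about 1/(1 − (C − 1)/107), which is 1.4% of the standard error with four communities and 2.4% with six. If the community ICC is near 0.01, that exceeds the gain. Stratifying largely avoids this cost. The regression in 3.20 also enters covariates by forward selection, which does not guarantee that community is included.

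**Conclusion.** The concern holds as a modest, avoidable loss of balance and precision. Section 3.10 ignores a known grouping factor that coincides with the nurse. At least one community split 2:1 or worse is a realistic outcome (about 25% with four equal communities, 70% with six), and more likely if sizes are unequal. Validity is not threatened. The excess standard error is under 1% at a community ICC of 0.01, about 3–6% at 0.05–0.10 and about 13% at 0.20. These figures rest on assumed community sizes and ICC. The split probabilities also assume the haemoglobin-level shares. The case for change rests on its low cost more than on the size of the gain.

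**What to change.** In 3.10, add community as a stratification factor beside mean household haemoglobin. Use smaller blocks, because strata will be smaller and a part-filled block of 8 or 12 balances poorly. If the level below 7.0 g/dL would leave near-empty strata, merge it with the next level for allocation only. In 3.20, include community and haemoglobin stratum as fixed terms in the primary haemoglobin model, outside the stepwise selection. Reconcile four communities (3.8.1, 3.8.2) with six (3.9, 3.14.1), since the number of strata depends on it.

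The cost is one more variable in the allocation program and a few degrees of freedom in the analysis. The downside is the loss of separate balance on the small severe level. Because households are recruited before the list is generated, smaller blocks do not open the usual route to selective enrolment. The required sample size does not change.
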